**List of Abbreviations**

LRTI Lower Respiratory Tract Bacterial Infection

LAMP Loop-mediated isothermal AMPlification

qLAMP quantitative Loop-mediated isothermal AMPlification

# Study Summary

| Title | Prospective, multi-center, clinical study of quantitative LAMP vs. routine culture/serological test for etiologic diagnosis in LRTI patients |
| --- | --- |
| Short Title | Etiologic Diagnosis of LRTI via LAMP |
| Protocol Number | 00001384 |
| Study design | Consecutive LRTI patients are planed to be enrolled in multi-centers, sputum samples from eligible subjects are planed to be applied to parallel tests of qLAMP and culture/serological test, the results and accuracy of both tests are to be compared and determined statistically. |
| Study Duration | Dec 2007-Dec 2008 |
| Study Center(s) | 21 centers—21 tertiary hospitals over 14 provinces of P. R. China agreed to participate. |
| Objectives | Evaluate the accuracy of qLAMP in etiology diagnosis of LRTI patients. |
| Number of Subjects | About 3000 LRTI patients |
| Diagnosis and Main Inclusion Criteria | Patients were suspected to have bacterial LRTI with typical diagnoses of pneumonia or bronchitis based on chest X-ray, as well as clinical symptoms and simple laboratory signs. |
| The evaluated test | Quantitative LAMP of 11 common bacteria in LRTI subjects. |
| Reference test | Routine bacterial culture/serological test |
| Statistical Methodology | Using SPSS version 17.0, the data were summarized in a receiver operating characteristic (ROC) curve to determine the diagnostic efficacy, the area under the curve (AUC) and its 95% confidence interval (95% CI) were calculated as a measure for the discriminative efficacy of the index test.  R software will be used to construct statistical model to explore to relationship between the result of both tests, and calculate cut-offs if necessary. |

# Introduction

This document is a protocol for a human research study. This study is to be conducted according to international standards of Good Clinical Practice, applicable government regulations and Institutional research policies and procedures.

## Background

Lower respiratory tract infections (LRTI) are a public health problem of major concern, which account for 12% & 16% of the inpatients in city and county hospitals of China. Beyond this, LRTI also importantly contribute to antibiotic overuse and allocation of health resources worldwide. . Many LRTI are caused by organisms that do not require antibiotics or could be safely treatment with narrow-spectrum antibiotics. Identifying the etiology of LRTI by traditional culture test assay needs at least 48-72hr. And there are a large proportion of cases with no pathogen identifying, either because the appropriate tests were not performed or the organism was missed. Thus, treatment of LRTI is generally empirical, with physicians reliant on previous etiology and microbiology studies to guide their choice of intervention, although each of these can be misleading. It is necessary to explore new, rapid and accurate diagnostic techniques.

A PCR-Chip assay for sepsis named prove-itTM was approved in Finland, which detects 31 pathogen bacteria in 3hours. But this non-quantitative method only work with blood or body fluid normally asepsis, while not sputum, the most convenient and routine specimen of LRTI, as many other similar methods . Real-time PCR, NASBA, LAMP, and many quantitative nuclear acid amplification methods had been successively applied in clinical virus detection, such as CMV, HCV, HBV, HIV. And some of these methods had been approved to be able to detect several pathogens simultaneously with perfect sensitivity and specificity in standard bacteria stains. While in the term of bacteria or fungi, these methods showed much more positive results in clinical sputum sample tests according to traditional culture assay. The discrepancies must be rationally explained before these methods to be applied in clinical.

## Index test

Loop mediated isothermal amplification (LAMP) is a single tube technique for the amplification of [DNA](http://en.wikipedia.org/wiki/DNA)[[1]](http://en.wikipedia.org/wiki/Loop-mediated_isothermal_amplification" \l "cite_note-0%23cite_note-0). It may be combined with a [reverse transcription](http://en.wikipedia.org/wiki/Reverse_transcription) step to allow the detection of RNA. LAMP is a novel approach to nucleic acid amplification which uses a single temperature incubation thereby obviating the need for expensive [thermal cyclers](http://en.wikipedia.org/wiki/Thermal_cyclers). Detection of amplification product can be by photometry for turbidity caused by increasing quantity of Magnesium pyrophosphate in solution [[2]](http://en.wikipedia.org/wiki/Loop-mediated_isothermal_amplification" \l "cite_note-1%23cite_note-1) or with addition of [SYBR green](http://en.wikipedia.org/wiki/SYBR_green), a color change can be seen without equipment.

The reaction can be followed in real-time either by measuring the turbidity [3] or the signals from DNA produced via fluorescent dyes that intercalate or directly label the DNA, and in turn can be correlated to the number of copies initially present. Hence, LAMP can also be quantitative. While LAMP is widely being studied for detecting infectious diseases such as tuberculosis, malaria [4], and sleeping sickness in developing regions, it has yet to be extensively validated for other common pathogens.

## Preclinical Data

Genomic sequences of 11 bacteria species, i.e. *Acinetobacter baumannii, Escherichia coli, Haemophilus influenzae, Klebsiella pneumoniae, Pseudomonas aeruginosa, Staphylococcus aureus, Stenotrophomonas maltophilia, Streptococcus pneumoniae*, *Legionella pneumophila, Mycoplasma pneumoniae* and *Chlamydophila pneumoniae* were retrieved from Genebank. Each primer set was designed based on the strategy described previously, and sensitivity, specificity and reproducibility of them were evaluated by quantified DNA from 27 species of bacteria. Quantitative LAMP assay was performed by real-time fluorescence detection modified from a previously published protocol.

Quantified DNA of the 11 tested bacteria, which was extracted and purified by QIAamp according to the manufacturer’s instructions, was serially diluted as positive control. Concentration of copy-number of genomic equivalents was calculated based on its genome size to plot standard curve. Then the equivalent copy numbers of the template DNA were determined based on the standard curves generated from quantified control DNA.

The sensitivity of each set of primers was determined by serially diluted each targeted DNA template as the consistently detectable minimal content (copies/μl DNA template), then traced to the titer of bacteria in sputum by the following equation:

Titer in sputum [copies/ml] = copies/μl (content in DNA template) × 100μl (template volume) / 0.5 ml (sputum volume)

The specificity of each set of primers were evaluated by quantified bacteria DNA of 27 species (8 targeted and 19 reference species, listed in Supplement Table 4) obtained as mentioned above, to exclude primer set show any cross reaction with other species DNA.

Serially diluted each targeted DNA templates were tested at least 8 times at different time and on different machines. The ranges of error were calculated to evaluate the reproducibility of our LAMP system.

Our primer sets for the 11 bacteria showed sensitivities to a titer of 103copies/ml in sputa and specificities where no detectable cross-reaction with DNA from 26 other bacterial species. The maximum range of titer from single standard DNA temple was less than 6 fold. These showed acceptable sensitivity, specificity and reproducibility of our LAMP system.

# Study Objectives

Primary Objective

To compare and determine the etiology diagnostic test accuracy of qLAMP test and routine bacteria culture/serological test for the etiology diagnosis in LRTI patients with sputum samples.

Secondary Objective

1. To compare results of qLAMP with the results of routine culture/serological test, or

Assess the relationship between the results of qLAMP and routine bacterial culture/serological test.

2. To evaluate the necessity of quantization and cut-off setting.

3. To explore heterogeneity in term of bacterial pathogens involved in LRTI.

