# Study Design and Procedures

The study will be conducted according to the following design and procedures in the flowchat:

Exclusion by no qualified sample

Exclusion by rectified diagnosis as non-infectious diseases or non-bacterial infections

Specimen collection and evaluation

men

ollection and evaluation

Consecutive suspected LRTI patients according to inclusion criteria

Informed Consent Form Signed

Clinical information input

Statistical analysis

1st day anticoagulated blood

1st day

sputum

1st day

sputum

3r day

sputum

2nd day

sputum

anticoagulated blood (at least 10days late)

)

LAMP & Culture in core lab

Culture in local hospital

Serological test in core lab

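### The primary objective compares the accuracy of qLAMP with that of culture/serology, but culture/serology is itself the reference test, so the plan cannot answer it

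*Protocol*

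**What the plan says.** The primary objective (Protocol, Study Objectives) is "To compare and determine the etiology diagnostic test accuracy of qLAMP test and routine bacteria culture/serological test". The Study design row of the Study Summary repeats it: "the results and accuracy of both tests are to be compared and determined statistically". The Objectives row of the same Summary is narrower: "Evaluate the accuracy of qLAMP in etiology diagnosis of LRTI patients". The Reference test row reads "Routine bacterial culture/serological test".

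Statistical Methods (5.2) plans a ROC curve, with AUC and 95% confidence interval, for the index test. It adds a model of the relationship between the two tests, with cut-offs if needed. It does not restate what the ROC curve is scored against, so the Summary's reference test is the only candidate.

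On the quality of that reference, the Background says of traditional diagnosis that "there are a large proportion of cases with no pathogen identifying, either because the appropriate tests were not performed or the organism was missed", and of amplification methods for bacteria or fungi that "these methods showed much more positive results in clinical sputum sample tests according to traditional culture assay". It adds that such discrepancies need a rational explanation before clinical use.

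**The concern.** A comparison of the accuracy of two tests needs a standard that is neither of them. Here one of the two tests is the standard. If the plan is run as written, one arm of the comparison is fixed at perfection, and any disagreement is booked as an error of the other arm.

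The Background expects disagreement mainly in one direction, with qLAMP positive and culture negative, and treats its meaning as an open question. The planned analysis closes that question by convention. At stake is whether the trial can report anything on its primary objective as worded, and how its qLAMP specificity and AUC may be read.

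**Working it through.** **1. Is there any other standard in the Protocol?**

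- Exclusion Criteria (3.2) uses a later diagnosis to remove non-infectious, viral, fungal, pneumocystis and TB cases. It does not assign a bacterial pathogen to those who remain.
- Statistical Methods (5.2) models one test against the other. That is not an independent truth.
- The flowchart in Study Design and Procedures shows "LAMP & Culture in core lab" and "Culture in local hospital", with sputum on days 1 to 3. No rule combines these cultures into a standard separate from the test under comparison.
- Sample Size (5.1) names an expected sensitivity for qLAMP only, which fits a one-test accuracy study.

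No pathogen-level standard other than culture/serology is defined.

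**2. Culture/serology scored against itself.** Every reference-positive is test-positive and every reference-negative is test-negative. Sensitivity = specificity = 100%, an identity that needs no assumption. Youden's index (sensitivity + specificity − 1) is 1.00, the maximum, so qLAMP can equal it but never exceed it.

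**3. Effect on qLAMP (illustration).** The Protocol gives no figure for the true accuracy of culture, so there is no stated figure to reproduce. All inputs are assumptions:

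- true prevalence π = 0.10 (5.1 expects positive rates of 5-15%);
- qLAMP sensitivity S = 0.95 (top of the 90-95% in 5.1) and specificity P = 0.98;
- culture specificity 100% and culture sensitivity C = 0.5, 0.6 or 0.8;
- results of the two tests independent given true status.

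The share of truly infected patients among culture-negatives is

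w = π(1−C) / [π(1−C) + (1−π)].

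Apparent sensitivity stays at S, because culture-positives are all truly infected. The other quantities are

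apparent specificity = [π(1−C)(1−S) + (1−π)P] / [π(1−C) + (1−π)]

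apparent AUC = (1−w)·AUC + w/2, with single-cut-point true AUC = (0.95 + 0.98)/2 = 0.965.

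| C | w | Apparent specificity | Apparent AUC |
|---|---|---|---|
| 0.5 | 0.05/0.95 = 0.0526 | 0.8845/0.95 = 93.1% | 0.941 |
| 0.6 | 0.04/0.94 = 0.0426 | 0.884/0.94 = 94.0% | 0.945 |
| 0.8 | 0.02/0.92 = 0.0217 | 0.883/0.92 = 96.0% | 0.955 |

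The loss is 2.0 to 4.9 points of specificity and 0.010 to 0.024 of AUC.

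**4. Effect on the comparison.** At C = 0.6 the true Youden indices are 0.60 for culture (0.60 + 1.00 − 1) and 0.93 for qLAMP (0.95 + 0.98 − 1). Scored against culture they become 1.00 and 0.95 + 0.940 − 1 = 0.89. The ranking reverses although the shift in qLAMP's own AUC is small.

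**5. Cut-off.** Under the same assumptions, culture-positives follow the distribution of the infected, and culture-negatives are a mixture with share w infected. Apparent Youden at any cut-off is therefore (1−w) times true Youden. It shrinks everywhere by the same factor, so the cut-off that maximises it does not move.

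**The case against.** The best defence is that the Protocol's intent is plain. The Objectives row speaks of qLAMP accuracy alone, the ROC analysis matches that, and the first secondary objective already covers comparison of results. On this reading the two-test wording is loose drafting. Part of this stands: the planned analysis does suit the narrower objective. But the formal primary objective and the Study design row both say otherwise. Because agreement has its own secondary objective, the primary one must mean more than agreement.

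A second defence is that the statistical analysis plan, not shown here, may supply a composite or model-based standard. The absence of such detail is indeed no finding. But the objective and the reference test are both fixed in the Protocol and are incompatible there, so an analysis plan could resolve the conflict only by departing from one of them.

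Third, if the reference pooled several cultures, a single culture could score below 100%. That is true, but the Protocol states no such rule.

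The objections to stronger readings hold. A reader might infer that every extra qLAMP detection becomes a false positive. qLAMP is quantitative and the need for a cut-off is a secondary objective, so only results at or above the cut-off count. A reader might also infer that a cut-off tuned to culture is pushed too high. Step 5 shows that this does not follow for a Youden criterion under the assumptions used, and the Protocol names no criterion. Finally, a large fall in positive predictive value might be quoted, but the Protocol does not plan that statistic.

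**Conclusion.** The plan is wrong as written on this point. The comparative primary objective cannot be answered with culture/serology as both comparator and reference, and the planned analysis could never show qLAMP to be better. This part rests on no assumption.

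The effect on qLAMP's own figures is illustrative. Under the inputs above, apparent specificity is 93.1-96.0% against a true 98%, and AUC is 0.941-0.955 against a true 0.965. The loss grows with prevalence and with the share of infections that culture misses, and the Protocol does not give that share.

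A reader might infer that qLAMP's accuracy is necessarily understated. The documents do not support that. The Background does not say that the extra positives are true infections, and it attributes unidentified cases partly to tests that were not done. If both tests pick up the same colonising organism in a patient whose infection has another cause, both are wrong about etiology, yet the pair is scored as a true positive. Apparent accuracy would then be inflated. Perfect culture specificity and conditional independence exclude this by assumption.

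**What to change.** Reconcile the Study Summary (Study design, Objectives and Reference test rows), the primary objective and Statistical Methods (5.2). Restate the primary objective and the ROC/AUC analysis as the accuracy of qLAMP relative to culture/serology, acknowledged as an imperfect reference. Report positive and negative percent agreement at any chosen cut-off, and make no claim of comparative accuracy from this analysis. The cost is wording and a more modest conclusion. No new samples or procedures are needed.

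Optionally, if comparative accuracy is to be kept, fit a latent-class model for the culturable species. It should state its dependence assumption and be read as estimating presence of the organism in sputum, not etiology. For species defined by serology, report agreement only.

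The model is feasible only if each patient has enough separate culture results. With three binary tests and two classes there are 1 + 3 + 3 = 7 parameters and 2³ − 1 = 7 degrees of freedom, so nothing is left to estimate dependence between cultures. The extracted flowchart has lost its arrows, so which sample goes to which laboratory must be confirmed first. The price is wider intervals that depend on the assumptions.

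A composite that counts any positive culture should not be used to judge culture's own accuracy, because it again makes culture its own reference.

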# Subject Selection

## Inclusion Criteria

Patients were suspected to have bacterial LRTI with typical diagnoses of pneumonia or bronchitis based on chest X-ray, as well as one of the following criteria:

(1) fever>38.50C,

(2) peripheral white blood cell count (WBC)>10.0×109/L and neutrophil % >60%,

(3) exacerbated dyspnea

(4) exacerbated sputum production or purulence.

## Exclusion Criteria

After informative diagnosis, patients rectified as one of the following:

(1) non-infectious diseases

(2) mainly infected by virus,

(3) mainly infected by fungi,

(4) mainly infected by pneumocystis

(5) mainly infected by TB

## Subject Recruitment and Screening

Potential bacterial LRTI patients were consecutively enrolled from 21 tertiary hospitals over 14 provinces in People’s Republic of China as the inclusion criteria, then samples will be collected to quality evaluation. Subjects with qualified samples will be applied to qLAMP and routine culture/serological test assay. Subjects adapt to exclusion criteria after informative diagnosis will be excluded.

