## Statistical Methods

Using SPSS version 17.0, the data were summarized in a receiver operating characteristic (ROC) curve to determine the diagnostic efficacy, the area under the curve (AUC) and its 95% confidence interval (95% CI) were calculated as a measure for the discriminative efficacy of the index test.

R software will be used to construct statistical model to explore to relationship between the result of both tests, and calculate cut-offs if necessary.

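### Patients found after testing not to have mainly bacterial disease are dropped, so accuracy is estimated in a set selected on final diagnosis, and section 5.3 defines a different set

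*Protocol*

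**What the plan says.** - **Entry (Inclusion Criteria, 3.1).** "Patients were suspected to have bacterial LRTI with typical diagnoses of pneumonia or bronchitis based on chest X-ray", plus one of four clinical or laboratory signs. Section 3.3 makes enrolment consecutive.
- **Testing (3.3).** "Subjects with qualified samples will be applied to qLAMP and routine culture/serological test assay".
- **Removal (3.3).** The next sentence reads: "Subjects adapt to exclusion criteria after informative diagnosis will be excluded". Section 3.2 introduces the list with "After informative diagnosis, patients rectified as one of the following" and names non-infectious disease and infection mainly by virus, fungi, pneumocystis or TB. The flowchart in section 4 has a matching box: "Exclusion by rectified diagnosis as non-infectious diseases or non-bacterial infections".
- **Use of the data.** The primary objective is "To compare and determine the etiology diagnostic test accuracy of qLAMP test and routine bacteria culture/serological test" in LRTI patients. Under section 5.2, "the data were summarized in a receiver operating characteristic (ROC) curve to determine the diagnostic efficacy", with AUC and its 95% CI, and cut-offs if needed.
- **Analysis population (5.3).** Membership depends on qualified samples and clinical information, and on having been randomized, although the study has no randomization. Final diagnosis is not mentioned.
- **Meaning of LRTI.** The List of Abbreviations defines it as a bacterial infection. The Background uses it more widely: "Many LRTI are caused by organisms that do not require antibiotics". That sentence goes on to infections for which narrow-spectrum antibiotics would do.

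**The concern.** Under sections 3.2 and 3.3, membership of the accuracy set is settled by a diagnosis that is not yet known when qLAMP would be used. The patients removed entered on the same criteria as those kept, so a clinician using the test could not set them aside.

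They are also an informative group for the study's own questions. The Background says that nucleic-acid methods find more positives in sputum than culture does and that this discrepancy has to be explained. Secondary objective 2 asks whether quantification and a cut-off are needed. Patients finally judged not to have mainly bacterial disease help to separate carriage from infection, and they leave before the ROC analysis and any cut-off.

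At stake is whether the reported AUC and cut-offs apply to the suspected patients who were enrolled or only to those later confirmed as bacterial. Because section 5.3 does not carry the exclusion, two analysts following the protocol could use different denominators for the primary estimate.

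**Working it through.** **Plan's own figures.** The protocol gives no exclusion share, no carriage rate and no specificity, so it has no figure for this effect to reproduce. It does give 1500 eligible patients, positive rates of 5-15% and sensitivity of 90-95% (5.1). Its range of 400-3000 patients comes without a stated precision and cannot be checked; this point does not depend on it.

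**1. Order of events.** Section 3.3 runs: enrol on suspicion, check the specimen, test, exclude after the diagnosis. The order rests on that sentence sequence and on the wording of 3.2. The flowchart text confirms the exclusion, but in extracted form does not show its position.

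**2. Negatives that remain.** Analysis concerns 11 separate bacteria. With 1500 retained, reference-negatives per pathogen number 1500 × (1 − 0.15) = 1275 to 1500 × (1 − 0.05) = 1425. These are patients with other bacteria or with no pathogen found. What is lost is the group without mainly bacterial disease.

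**3. Specificity (all inputs assumed).** Let k be the share of reference-negatives dropped, f0 the qLAMP positivity in retained negatives and f1 that in dropped negatives. Full-group specificity = 1 − [(1 − k)·f0 + k·f1]. With f0 = 0.05 the retained set reports 95.0%.
- k = 0.30, f1 = 0.10: 1 − (0.035 + 0.030) = 93.5%
- k = 0.10, f1 = 0.10: 1 − (0.045 + 0.010) = 94.5%
- k = 0.30, f1 = 0.05: 1 − (0.035 + 0.015) = 95.0%, no change
- k = 0.30, f1 = 0.025: 1 − (0.035 + 0.0075) = 95.75%, so the retained set understates it

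**4. AUC and cut-off (all inputs assumed).** Take normal distributions with SD 1: positives at mean 2, retained negatives at 0, excluded negatives at δ. The positive rate is 10%, and 30% of tested patients are excluded, all reference-negative. Tested = 1500/0.7 = 2143, so excluded = 643. Their weight among negatives is w = 643/(1350 + 643) = 0.323. Retained AUC = Φ(2/√2) = 0.921, with Youden cut-off 1.00. Full AUC = (1 − w)·0.921 + w·Φ((2 − δ)/√2).
- δ = −0.5: AUC 0.934, cut-off 0.92
- δ = 0: AUC 0.921, cut-off 1.00
- δ = 0.5: AUC 0.900, cut-off 1.08
- δ = 1.0: AUC 0.869, cut-off 1.12

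**5. PPV.** Sensitivity 0.90 and the positive rates are from 5.1. The rest is assumed: 10% false positives in both groups, and 30% of tested patients excluded, all reference-negative.
- Positive rate 5%: true positives 1500 × 0.05 × 0.90 = 67.5, false positives 1425 × 0.10 = 142.5. Retained PPV = 67.5/210 = 0.321. The 643 excluded add 64.3 false positives, so full PPV = 67.5/274.3 = 0.246.
- Positive rate 15%: 202.5/(202.5 + 127.5) = 0.614 retained, and 202.5/(330 + 64.3) = 0.514 in full.
- With 10% excluded, the full values are 0.298 and 0.584.

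**6. Positives if 1500 became the total.** With 30% non-bacterial (assumed), 1500 × 0.7 = 1050 would be bacterial. Positives per pathogen would fall from 75 to 52.5 at 5%, and from 225 to 157.5 at 15%.

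**The case against.** The strongest reply is that the List of Abbreviations makes LRTI bacterial by definition and the objective asks which bacterium is present. The exclusion would then only define the target condition. This has weight: title and objective speak of LRTI patients, not of suspected ones. But enrolment is on suspicion, the Background uses the term more widely, and section 5.3 does not restrict by final diagnosis. The target population is therefore unsettled.

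Several stronger readings are tempting, and the documents do not support them:
- **The reference-negatives are gone.** They are not; step 2 leaves 1275 to 1425 per pathogen.
- **Accuracy is biased in a known direction.** With equal qLAMP distributions in excluded and retained negatives, specificity, AUC and the Youden cut-off do not change. Otherwise either direction is possible.
- **Half the patients are excluded.** The Study Summary's figure of about 3000 against 1500 eligible might suggest this. Unqualified specimens are dropped too, and the two numbers may simply be inconsistent.
- **qLAMP results steer the final diagnosis.** qLAMP is run in a core laboratory and nothing shows its results reaching the diagnosing clinicians. Culture/serology could inform the diagnosis, but the protocol states no rule either way.
- **A planned PPV endpoint is wrong.** PPV is not a named endpoint.

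It is also fair to say that infection mainly by another organism allows a positive bacterial culture. Some excluded patients may be reference-positive, so sensitivity could be affected and the PPV calculation would change.

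**Conclusion.** The concern stands as a question of who is in the accuracy set. The protocol selects that set on a diagnosis made after enrolment and testing, loses an informative part of the reference-negatives, and contradicts its own analysis-population section. The estimates would describe patients with a final bacterial diagnosis, not the consecutive suspected patients enrolled.

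The size cannot be determined from the documents. Under the assumed inputs, the specificity difference ran from 1.5 points too high to 0.75 points too low. AUC was 0.921 in the retained set against 0.869 to 0.934 in the full set. These results need a difference in qLAMP distributions between excluded and retained negatives. The PPV overstatement needs only that the excluded are mostly reference-negative with some false positives, and it matters only if a PPV is reported.

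**What to change.** - Make the primary accuracy set all consecutively enrolled suspected-LRTI patients with a qualified specimen and both test results, classified per pathogen by their own culture/serology result.
- Turn the 3.2 list into a recorded final-diagnosis variable. Report counts and qLAMP positivity in each final-diagnosis group.
- Keep the set with a final bacterial diagnosis as a sensitivity analysis.
- Align the List of Abbreviations, sections 3.2 and 3.3, the flowchart in section 4 and section 5.3, so that one definition of LRTI and one analysis population remain.
- Keep 1500 as the number with a final bacterial diagnosis and add the other tested patients to it, so that positives per pathogen do not fall.

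The cost is mainly rewording, because under 3.3 these patients are already tested. Two downsides should be accepted openly. Accuracy may look less favourable. The second blood sample, due at least 10 days later, may be missing in some re-diagnosed patients, so their serological classification would be incomplete and should be counted.
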